## **10.3 Statistical Method**

### **10.3.1 General Considerations**

Summary statistics including the number of patients, mean, standard deviation, median, minimum and maximum, will be presented for all continuous variables. For categorical variables, per category, the absolute counts (n) and percentages (%) of patients with data, and if appropriate, the number of patients with missing data, will be presented.

All statistical analysis will be performed by using SAS 9.4 or later version.

### **10.3.2 Subject Disposition**

The number of subjects who are enrolled, completed and discontinued will be summarized in each group. The reason for discontinuation will be analyzed as well.

The demographic characteristics will be summarized and described by treatment group.

### **10.3.3 Immunogenicity Analysis**

ANCOVA model will be employed to analyze post-vaccination GMT. In the model, log-transformed GMT after vaccination will be included as dependent variable, pre-vaccination GMT after log-transformation is the covariate and group assignment and sequential vaccination time (1-3 months, 4-6 months and  $\geq 6$  months after the sequential dose) are the fixed effect. The adjusted LSMean in each arm and difference between the two groups together with 95% confidence interval (CI) will be estimated from the model. After inverse log-transformation, the adjusted GMT after vaccination and GMT ratio together with 95% CI between treatment and control groups will be derived. If the lower bound of 95%CI is larger than 0.67, the non-inferiority result will be concluded.

The 4-fold rise, and the proportions of antibody titered  $\geq 1:16$ ,  $\geq 1:32$  and  $\geq 1:64$  after vaccination in both vaccine and placebo groups will be estimated. The corresponding 95% CIs will be derived from Clopper-Pearson method. The difference between the two groups and their 95% CIs will be estimated by CMH method including the stratification factor (sequential vaccination time). If the lower bound of 95%CI in 4-fold rise rate is larger

than -10%, the non-inferiority will be concluded.

The descriptive statistics, including geometric mean and corresponding 95% CI, are employed to summarize GMT and GMI after sequential dose. The t-tests after log transformation will be compared between the two groups.

The reverse cumulative distribution plot is to depict the pre- and post-vaccination antibody data in the vaccine and placebo groups.

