### **4.4 Trial Hypothesis**

① The 4-fold rise of neutralizing antibody of recombinant COVID-19 vaccine (CHO cells) after sequential vaccination with one dose of vaccine is not inferior to that of inactivated COVID-19 vaccine (Vero cells), and the threshold of non-inferiority is -10%. If the lower bound of 95% CI is  $>-10\%$ , the hypothesis of non-inferiority in 4-fold rise between vaccine and control groups will be concluded.

② After sequential vaccination of one dose of recombinant COVID-19 vaccine (CHO cells),

GMT is not inferior to COVID-19 inactivated vaccine (Vero cells), and the non-inferior threshold is 2/3 (GMT ratio; the difference on log10 scale is -0.176). If the lower bound of GMT ratio 95% CI is  $> 2/3$ , the hypothesis of non-inferiority in GMT between vaccine and control groups will be concluded.

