### **10. STATISTICAL CONSIDERATIONS**

#### **10.1 Sample Size Considerations**

Assume 4-fold rise rate after sequential vaccination achieve 85%, 208 subjects in each arm will be required to have 80% power to conclude non-inferiority with margin of -10% and one-sided significance level of 2.5% using Miettinen & Nurminen method.

Equal GMT after sequential immunization is assumed, and standard deviation of GMT after log10 transformation is considered to be 0.7. 250 subjects in each arm will be required to have 80% power to conclude non-inferiority with margin of 2/3 and one-sided significance level of 2.5%.

Considering about 15%~20% drop-out rate, 600 subjects in three sequential cohorts (1-3 months, 4-6 months and ≥6 months after 2 doses), and 1800 subjects (900 subjects in test and control groups respectively) in total are planned to enroll.

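### Protocol 10.3.3 writes the GMT non-inferiority limit as 0.67, apparently a rounding of the 2/3 in 4.4 and 10.1; read literally it is a slightly stricter rule (minor)

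*Protocol*

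**What the plan says.** The limit for the GMT comparison appears in three places in the Protocol.

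- **4.4 Trial Hypothesis:** "the non-inferior threshold is 2/3 (GMT ratio; the difference on log10 scale is -0.176". Non-inferiority is concluded when the lower 95% confidence bound of the ratio exceeds 2/3.
- **10.1 Sample Size Considerations:** "250 subjects in each arm will be required to have 80% power to conclude non-inferiority with margin of 2/3".
- **10.3.3 Immunogenicity Analysis**, directly after the ANCOVA is described: "If the lower bound of 95%CI is larger than 0.67, the non-inferiority result will be concluded".

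Section 10.6 makes the GMT result one of two conditions, with the 4-fold rise, that must both be met before overall non-inferiority is concluded. The Protocol does not say that 0.67 stands for 2/3, or which section governs.

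**The concern.** Section 10.3.3 is the rule a programmer would code against the back-transformed confidence bound. Taken at face value it differs from the hypothesis in 4.4 and from the margin behind the sample size. A bound that lands between the two values passes one section and fails the other. Because of 10.6, that would decide the overall claim as well. A borderline result would then have to be settled after the data are seen, which a pre-specified margin is meant to prevent.

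**Working it through.** **Inputs, all from Protocol 10.1 unless noted**

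- SD of log10 titre: 0.7 ("transformation is considered to be 0.7").
- True GMT ratio: 1 ("Equal GMT after sequential immunization is assumed").
- Test level: one-sided 2.5%, so z = 1.960.
- Target power: 80%, so z = 0.8416.
- Allocation: 1:1 (4.2).
- Limits compared: 2/3 (4.4, 10.1) and 0.67 (10.3.3).

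**Step 1. The two limits on the log10 scale**

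- log10(2/3) = -0.17609
- log10(0.67) = -0.17393

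The -0.176 printed in 4.4 belongs to 2/3. For 0.67 it would have been -0.174.

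**Step 2. Reproduce the protocol's 250 per arm**

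n per arm = 2 × (1.960 + 0.8416)² × SD² / margin² = 2 × 7.849 × 0.49 / margin²

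- At 2/3: 7.692 / 0.17609² = 248.1, so 249. The noncentral-t version gives 250, with power 80.15%. The stated figure reproduces.
- At 0.67: 7.692 / 0.17393² = 254.3, so 255. The noncentral-t version gives 256.

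**Step 3. Power in a single cohort at 250 per arm**

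SE = 0.7 × √(2/250) = 0.06261, and power = Φ(margin/SE − 1.960).

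- At 2/3: Φ(2.8125 − 1.960) = 80.3%
- At 0.67: Φ(2.7780 − 1.960) = 79.3%

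By noncentral t these are 80.2% and 79.2%. Either way the loss is about 1 point.

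**Step 4. Power in the pooled ANCOVA**

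The model in 10.3.3 takes all three cohorts together, with vaccination interval as a fixed effect. With 900 per arm and the upper end of the protocol's drop-out range, n = 900 × 0.80 = 720 and SE = 0.7 × √(2/720) = 0.03689.

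- At 2/3: Φ(4.773 − 1.960) = 99.75%
- At 0.67: Φ(4.714 − 1.960) = 99.71%

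The difference is 0.05 point. No allowance is made for variance removed by the baseline covariate.

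**Step 5. Sensitivity to the true ratio**

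The ratios 0.9 and 0.8 are illustrative assumptions; the protocol assumes 1. The chance that the lower bound falls between the two limits is:

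| True GMT ratio | 250 per arm | 720 per arm |
|---|---|---|
| 1.0 | 1.0% | 0.05% |
| 0.9 | 1.4% | 0.7% |
| 0.8 | 1.1% | 2.3% |

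**Step 6. Type I error under the 0.67 rule when the true ratio is exactly 2/3**

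The critical value rises by (0.17609 − 0.17393)/SE.

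- 250 per arm: 1.960 + 0.035 = 1.995, giving 2.3%.
- 900 per arm: 2.1%.

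Both are below the nominal 2.5%. Because 0.67 is the higher limit, 10.3.3 can never declare non-inferiority that 4.4 would refuse.

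**The case against.** The strongest reply is that there is only one margin here, written to two decimals in one place. 2/3 rounds to 0.67, and 4.4 rounds too when it prints -0.176 for -0.17609. The section that defines the hypothesis and the section that sizes the trial agree on 2/3, and nothing suggests that a second margin was chosen. As an account of intent this stands.

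The reply also holds on size. The protocol's own uncertainties move power at least as much as the rounding does. Of 300 enrolled per arm in a cohort, 15% drop-out leaves 255, where power is 81.1% at 2/3 and 80.1% at 0.67. At 20% drop-out 240 remain, and the figures are 78.7% and 77.7% (normal formula). An SD of 0.71 in place of 0.7 would by itself require 2 × 7.849 × 0.71² / 0.17609² = 255.2, so 256 per arm. That is as large a shift as the one from 2/3 to 0.67.

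The reply does not remove the mismatch. A decision threshold is applied literally, and 0.67 is not 2/3. The SAP is not at hand, so it cannot be assumed to settle the matter: one that copied 10.3.3 would carry the stricter limit forward, and one that used 2/3 would depart from the protocol's written analysis rule.

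**Conclusion.** The wording in 10.3.3 is inexact and should be corrected, but the point is minor. Bounds above 2/3 and up to 0.67 are classified differently by 4.4 and 10.3.3, always in the conservative direction. Under the protocol's assumptions (SD 0.7, equal GMTs) the cost is about 0.05 point of power in the pooled ANCOVA at 720 per arm, and about 1 point at 250 per arm in one cohort.

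Three stronger readings are tempting, and the document supports none of them.

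- *The protocol deliberately sets two different margins.* The -0.176 in 4.4 and the margin in 10.1 both point to 2/3, and 0.67 is that number rounded. The 250 per arm fits 2/3 best, although it lies too close to the 255 or 256 for 0.67 to be proof by itself.
- *About 1 trial in 100 would change verdict on the main GMT test.* That figure belongs to a single cohort at 250 per arm, and 10.4 lists the cohort analyses as subgroup analyses. The rule in 10.3.3 is attached to the pooled model, where the figure is 0.05% at equal GMTs. It reaches about 2% only at a true ratio near 0.8, which the protocol does not assume.
- *The sample size is wrong.* Section 10.1 claims 80% power for 2/3 only, and that claim reproduces.

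**What to change.** In Protocol 10.3.3, replace 0.67 with 2/3, stated as a lower 95% confidence bound of the GMT ratio above 2/3 (log10 difference > -0.1761), and say that the unrounded bound is compared with it. The second part matters: if the bound were itself rounded to two decimals and tested against 0.67, the smallest passing value would be 0.68, so the effective limit would be 0.675.

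The cost is one figure and one clause. No sample size, power statement or other limit changes. The edit should be made before unblinding, so that the choice of limit cannot appear to depend on the result.

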#### Immunogenicity Observation:

Blood samples of all the subjects will be collected before the vaccination of sequential dose and 14 days, 28 days, 3 months, 6 months, 9 months and 12 months after sequential vaccination for detection of neutralizing antibodies and anti-protein specific IgG antibodies.

Collect 12.5ml blood samples of all the subjects and separate serum. Neutralizing antibody will be determined by microdose cytopathogenic efficiency (CPE) assay and specific IgG antibody will be tested by enzyme-linked immunosorbent assay (ELISA).

Time points of blood sample collection is described in Table 1 Sample Size and Procedures of Clinical Trial.

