### **4.3. Study Endpoint**

#### **4.3.1 Immunogenicity Endpoint:**

##### **Primary Endpoints:**

GMT and 4-fold rise of anti-SARS-CoV-2 neutralizing antibody 14 days after sequential vaccination of one booster dose;

GMT and 4-fold rise of anti-SARS-CoV-2 neutralizing antibody 28 days after sequential vaccination of one booster dose.

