#### **10.2 Analysis Set**

Full Analysis Set (FAS): It includes all randomized participants who follow ITT principle, receive 1 dose of vaccine, and have valid immunogenicity data before the first dose.

Per-Protocol Set (PPS): It includes all participants who do not violate the inclusion criteria/exclusion criteria, receive 1 dose of vaccine, and have both valid pre- and post-vaccination immunogenicity data. PPS will be defined for immunogenicity evaluations 14 and 28 days after sequential vaccination, respectively.

Immunogenicity Persistence Set (IPS): It include the participants who are collected

with blood samples at each time point for immunogenicity persistence evaluation and with valid antibody data. Define the IPS for immunogenicity for 3, 6, 9, 12, 18 and 24 months after sequential immunization respectively.

Safety Set (SS): It includes all participants who receive one dose of vaccination.

In immunogenicity analysis, the participant who takes the vaccine erroneously will be included as randomized, and the safety data will be analyzed as treated.

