#### **10.6 Multiplicity**

Only when both non-inferiority conclusion in 4-fold rise and GMT after vaccination between treatment and control groups are achieved, the non-inferiority between the two groups will be concluded finally. Therefore, no multiplicity adjustment is required here.

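### The 4-fold-rise comparison in 10.3.3 is valid but leaves out the pre-booster titre already used for GMT; adding it costs only analysis wording and may narrow the cohort-level intervals

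*Protocol*

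**What the plan says.** The primary endpoints in protocol 4.3.1 pair GMT with the 4-fold rise at each of two visits; the day-14 entry is "GMT and 4-fold rise of anti-SARS-CoV-2 neutralizing antibody 14 days after sequential vaccination of one booster dose", and day 28 is worded the same way. Section 10.6 requires success on both measures: "Only when both non-inferiority conclusion in 4-fold rise and GMT after vaccination between treatment and control groups are achieved".

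Section 10.3.3 treats the two differently. GMT is analysed by ANCOVA, where "pre-vaccination GMT after log-transformation is the covariate and group assignment and sequential vaccination time" enter the model. The 4-fold rise is compared with sequential vaccination time as the only adjusting factor: "The difference between the two groups and their 95% CIs will be estimated by CMH method including the stratification factor (sequential vaccination time").

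The pre-booster titre is available. Section 4.2 states: "Blood samples of all the subjects will be collected before the vaccination of sequential dose". In section 10.2, FAS members must "have valid immunogenicity data before the first dose", which I read as before the single study dose, and the PPS requires valid data both before and after vaccination.

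Section 10.1 sizes the 4-fold rise at 208 per arm, without covariates, at a "one-sided significance level of 2.5% using Miettinen & Nurminen method".

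**The concern.** A 4-fold rise is a threshold on the difference between log post-booster and log pre-booster titre. Unless the slope of post on pre is close to 1, a subject's starting titre predicts whether the threshold is reached; with a slope below 1, subjects who start high are less likely to reach it. Defining the endpoint relative to baseline does not adjust the comparison for baseline. Stratifying by cohort removes baseline differences between cohorts, but not the spread of baseline, or a chance imbalance between arms, within a cohort.

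The protocol treats baseline as worth adjusting for in one co-primary and leaves it out of the other. What is at stake is some interval width, and protection against chance imbalance, on the 4-fold rise. The validity of the comparison is not in question.

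**Working it through.** **Inputs from the protocol.** 4-fold-rise rate 85% (taken as equal in both arms), margin -10 points, one-sided 2.5%, 80% power, 208 per arm, log10 titre SD 0.7, drop-out 15 to 20% (all 10.1); 300 per arm per cohort and 900 per arm overall. At 20% drop-out these become 300 × 0.8 = 240 and 900 × 0.8 = 720.

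**Inputs assumed.** SD of the log10 pre-booster titre, 0.4 to 0.6; pre/post correlation r, 0.1 to 0.6. The protocol gives neither. The SD of 0.7 is applied to the post-booster titre.

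**Step 1: the plan's own figure.** With rates restricted to a 10-point difference (0.787 and 0.887):

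n = [(1.960 × √(0.787×0.213 + 0.887×0.113) + 0.842 × √(2×0.85×0.15)) / 0.10]² = [(1.960×0.517 + 0.842×0.505) / 0.10]² = 206.9, so 207 per arm.

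This reproduces the stated 208, at which power is 80.2%. The sizing takes no credit for baseline adjustment.

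**Step 2: precision without adjustment.** SE = √(2×0.85×0.15/n); power = Φ(0.10/SE − 1.96).

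- One cohort, n = 240: SE 3.26 points, 95% half-width 6.4 points, power 86.6% (85.6% by the restricted formula of step 1).
- Pooled, n = 720: SE 1.88 points, half-width 3.7 points, power 99.96% (99.95% by the restricted formula).

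**Step 3: effect of adding log pre-titre.** In large samples the variance of the standardised risk difference is multiplied by 1 − R², where R² is the share of the variance of the 4-fold-rise indicator (0.85 × 0.15) explained by the pre-titre. With bivariate normal log titres, the chance of a rise given the pre-titre is a normal probability whose slope on pre-titre is (r × 0.7 / pre-SD) − 1. When r × 0.7 equals the pre-SD, that slope is zero and adjustment gains nothing.

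| Pre-titre SD | r | Variance removed | Half-width, n = 240 | Power, n = 240 |
|---|---|---|---|---|
| none (unadjusted) | – | – | 6.4 | 86.6% |
| 0.4 | 0.6 | 0.05% | 6.4 | 86.6% |
| 0.5 | 0.4 | 4.7% | 6.2 | 88.2% |
| 0.5 | 0.2 | 10.3% | 6.1 | 90.0% |
| 0.6 | 0.1 | 18.9% | 5.8 | 92.6% |

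Simulated trials comparing the logistic-standardised difference with the stratified difference in these four settings gave variance ratios of 1.00, 0.95, 0.89 and 0.80, in agreement with the formula. A wider assumed range (pre-SD 0.3 to 0.7, r 0 to 0.7) gives reductions of 0 to 28%.

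**Step 4: the pooled test.** In the most favourable row above, the half-width at 720 per arm goes from 3.7 to 3.3 points. Power is already 99.96%, so the pooled decision hardly changes under the planning assumptions.

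**The case against.** The strongest defence is that nothing is broken. The CMH difference is stratified by the randomisation factor and gives a risk difference on the scale of the margin. The endpoint is already relative to each subject's own baseline, and the sample size never counted on adjustment. The gain cannot be derived from the documents and may be zero. All of that stands; none of it shows a cost to adjusting.

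Three stronger readings are tempting, and the documents do not support them.

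- **A reader might infer that the current method puts the whole non-inferiority conclusion at risk, because both co-primaries must succeed.** At 85% in both arms and 720 per arm, the pooled 4-fold-rise test has about 99.96% power unadjusted. Even a single cohort, at about 87%, is above the 80% target.
- **A reader might infer that the CMH interval inflates the one-sided error.** For a simple Wald interval in one cohort of 250 per arm at the -10% boundary, exact enumeration gives 2.6%, 3.0% and 3.9% at control rates of 85%, 95% and 99%. The 3.9% needs a 99% control rate, which the protocol does not assume for the 4-fold rise, and an interval type that 10.3.3 does not name. A simulated three-stratum Mantel-Haenszel difference at 240 per arm per stratum gave 2.55% at the planning rate of 85%.
- **A reader might infer that sizing by Miettinen-Nurminen and analysing by CMH is a contradiction.** It is not: an unstratified formula sizes each cohort and a stratified estimator serves the pooled comparison. Using stratified Miettinen-Nurminen for the unadjusted analysis would be tidier, but nothing requires it.

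**Conclusion.** The point holds as an inexpensive improvement. The planned analysis is valid, but it leaves out a baseline variable that the same section uses for the other co-primary and that every FAS and PPS subject has. Adding it would cut the variance of the 4-fold-rise difference by roughly 0 to 20% and would correct for chance baseline imbalance within cohorts. The benefit falls mainly on the cohort-level analyses of 10.4.

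The size rests on assumed pre-titre SDs of 0.4 to 0.6 and correlations of 0.1 to 0.6, on bivariate normal log titres with a post-booster SD of 0.7, on an 85% rise in both arms, and on large-sample variance. If post-booster titre tracks pre-booster titre with a slope near 1, the gain is nil.

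**What to change.** In 10.3.3, estimate the 4-fold-rise difference as a standardised (marginal) risk difference from a logistic model with arm, sequential vaccination time and log pre-booster titre, with a robust or bootstrap 95% CI compared with -10%. Within a cohort, drop the cohort term. The marginal form matters: it keeps the estimand and the margin, which a conditional odds ratio would not.

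Keep the stratified unadjusted difference as a sensitivity analysis, either CMH as now or stratified Miettinen-Nurminen to match 10.1. Fix the wording before unblinding.

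The cost is a change of analysis text and standard code. The sample size, the margin and the data collection stay as they are.

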##### **Secondary Endpoints:**

GMT of anti-SARS-CoV-2 IgG antibody, 4-fold rise, GMI and proportions of neutralizing antibody titered  $\geq 1:16$ ,  $\geq 1:32$  and  $\geq 1:64$  before vaccination and 28 days after vaccination of sequential booster dose.

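### Section 10.3.3 adds unstratified t-tests on log GMT and log GMI beside its own ANCOVA; they are never meaningfully more precise and usually less so, though the primary conclusion does not depend on them.

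*Protocol*

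**What the plan says.** Under section 4.3.1, GMT of neutralizing antibody is a primary endpoint at day 14 ("GMT and 4-fold rise of anti-SARS-CoV-2 neutralizing antibody 14 days after sequential vaccination of one booster dose") and again at day 28. GMI appears among the secondary endpoints: "GMT of anti-SARS-CoV-2 IgG antibody, 4-fold rise, GMI and proportions of neutralizing antibody".

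Section 10.3.3 first sets the main GMT analysis: "ANCOVA model will be employed to analyze post-vaccination GMT". Its terms are given as "pre-vaccination GMT after log-transformation is the covariate and group assignment and sequential vaccination time". The decision rule follows directly from the interval for the adjusted GMT ratio: "If the lower bound of 95%CI is larger than 0.67, the non-inferiority result will be concluded". Section 4.4 states the GMT hypothesis as non-inferiority only.

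A later paragraph of section 10.3.3 says that descriptive statistics "are employed to summarize GMT and GMI after sequential dose", and then adds: "The t-tests after log transformation will be compared between the two groups". It names no covariate, stratum, margin or purpose for these tests.

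Section 4.6.1 stratifies randomisation by sequential vaccination time. Section 10.3.3 carries that factor into the ANCOVA and into the CMH analysis of proportions, but not into the t-tests. Section 10.4 repeats the immunogenicity analysis within each of the three cohorts.

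**The concern.** The section already contains a model that uses the baseline titre and the stratification factor. The t-tests use the same subjects for the same arm contrast and leave some of that information out.

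- **GMT:** the t-test uses neither baseline nor cohort, so any variance they explain stays in the error term.
- **GMI:** log GMI is the log post-dose titre minus the log pre-dose titre. A t-test on it does use baseline, but with the slope fixed at 1 instead of estimated, and without the cohort term. No other between-group test of GMI is stated.

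At stake is precision in reported comparisons, and two p-values for the GMT contrast with no stated order between them. The non-inferiority decision is not at stake. This is also not a detail left open for a later document: the protocol names a specific test, and it is the weaker of the two.

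**Working it through.** **1. The plan's own figure.** Section 10.1 gives SD 0.7 on log10, true ratio 1, margin 2/3 (0.1761 on log10), 80% power and one-sided 2.5%.

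n per arm = 2 × 0.7² × (1.960 + 0.842)² / 0.1761² ≈ 248.1, rounded up to 249. With the noncentral t distribution for an unadjusted two-sample t-test it is 250 (power 80.2%). The stated 250 is reproduced, and it takes no credit for covariates.

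**2. GMT: t-test against ANCOVA.** The t-test standard error is 0.7 × √(2/n). The ANCOVA's is that value times √(1 − R²), where R² is the share of log-titre variance explained by baseline and cohort. The protocol gives no R², so 0.10 to 0.50 is assumed.

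| R² (assumed) | t-test CI width / ANCOVA CI width = 1/√(1 − R²) |
|---|---|
| 0.10 | 1.05 |
| 0.25 | 1.15 |
| 0.50 | 1.41 |

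In absolute terms, at 750 per arm (3 × 250) the t-test standard error is 0.7 × √(2/750) = 0.0361. The 95% limits are then the ratio multiplied or divided by 10^(1.96 × 0.0361) = 1.18. At R² = 0.25 the ANCOVA gives 0.0313 and a factor of 1.15. In one cohort at 250 per arm the factors are 1.33 and 1.28.

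**3. GMI: the two analyses estimate the same contrast.** Write the ANCOVA on change as post − pre = a + b·group + c·pre + cohort. Moving pre to the right gives post = a + b·group + (c + 1)·pre + cohort. The arm effect b is identical, so the ANCOVA already stated also supplies the adjusted GMI ratio. The t-test on log GMI estimates the same contrast with c forced to 0 and no cohort term.

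**4. GMI: size of the loss.** Assumptions, none of them in the protocol except the post-dose SD: pre-dose SD 0.5, post-dose SD 0.7 (both within cohort), correlation ρ from 0.1 to 0.7, three equal cohorts with baseline means 1.5, 1.2 and 0.9 log10.

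- Variance of change within cohort: 0.25 + 0.49 − 2ρ(0.5)(0.7) = 0.74 − 0.70ρ.
- ANCOVA residual variance: 0.49(1 − ρ²).
- Extra variance in the pooled t-test if post-dose means are equal across cohorts: the fold rise then varies by cohort, adding (0.3² + 0² + 0.3²)/3 = 0.06.
- Extra variance if the mean fold rise is equal across cohorts: 0.

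The standard error ratio is the square root of the variance ratio.

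| ρ | ANCOVA variance | SE ratio, equal post-dose means | SE ratio, equal fold rise |
|---|---|---|---|
| 0.1 | 0.485 | √(0.73/0.485) = 1.23 | √(0.67/0.485) = 1.18 |
| 0.3 | 0.446 | √(0.59/0.446) = 1.15 | √(0.53/0.446) = 1.09 |
| 0.5 | 0.368 | √(0.45/0.368) = 1.11 | √(0.39/0.368) = 1.03 |
| 0.7 | 0.250 | √(0.31/0.250) = 1.11 | √(0.25/0.250) = 1.00 |

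The loss therefore runs from about 0% to 23%. At ρ = 0.7 the best-fitting slope is 0.7 × 0.7/0.5 = 0.98, almost the 1 that the t-test imposes, so any remaining loss comes from the missing cohort term. The last column also applies to the by-cohort analyses of section 10.4, where there is no cohort term to omit.

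**The case against.** The strongest reply is that the t-tests decide nothing. The rule for GMT stands on the ANCOVA interval, section 10.6 builds the overall conclusion from the two non-inferiority results, and the t-tests sit in a paragraph that opens with descriptive statistics. The role of supportive tests could also be settled in a statistical analysis plan that is not shown. This stands as far as the primary conclusion goes. It does not remove the point, because a between-group t-test is inferential and the protocol specifies it without a role.

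Four stronger readings are tempting, and the document does not support them.

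- **A rival test of the primary endpoint.** No threshold or claim is attached to the t-test, so it cannot overturn the ANCOVA result.
- **A GMI test that ignores baseline.** A change score contains baseline. The loss comes from the fixed slope and the missing stratum, and under some inputs it is nil.
- **A missing ordered route to superiority.** No objective, endpoint or hypothesis claims superiority, so no hierarchy is owed.
- **A looser test that would carry a claim.** A test with a larger standard error is less likely to declare a difference. Error rises only if a difference were claimed on whichever of the two tests succeeds: in simulation (750 per arm, cohort shift 0.2 log10, ρ from 0 to 0.7) one-sided error was about 2.7% to 3.8%, against a nominal 2.5%. The protocol plans no such use.

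**Conclusion.** The point holds as a minor, cost-free improvement in precision and consistency. Apart from a negligible difference in degrees of freedom, the t-tests are no more precise than the plan's own ANCOVA, and they are less precise whenever baseline or cohort explains variance that the t-test leaves in the error.

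For GMT the interval is about 5%, 15% and 41% wider at an assumed R² of 0.10, 0.25 and 0.50. For GMI the standard error excess is about 0% to 23%. The upper end needs a low pre-post correlation and equal post-dose means across cohorts; the lower end needs a correlation near 0.7 and equal fold rise. These inputs are assumptions, since the protocol states only the post-dose SD of 0.7. Sample size and the non-inferiority conclusion are unaffected.

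**What to change.** In section 10.3.3:

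- Delete the t-test sentence.
- State that every between-group comparison of GMT and GMI, for neutralizing and IgG antibody, uses the ANCOVA already described (log baseline, group, sequential vaccination time).
- State that the sequential vaccination time term is omitted in the by-cohort analyses of section 10.4.
- Keep the unadjusted geometric means and their 95% CIs, labelled as descriptive only.

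For a given antibody and time point, the adjusted GMI ratio equals the adjusted GMT ratio, so one estimate serves both and the text can say so.

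Cost: one sentence replaced. Baseline titres and cohort are already collected, and the sample size and the hypotheses in section 4.4 stay as they are.
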